# Can metformin relieve tibiofemoral cartilage volume loss and knee symptoms in overweight knee osteoarthritis patients? Study protocol for a randomized, double-blind, and placebo-controlled trial

**DOI:** 10.1186/s12891-022-05434-2

**Published:** 2022-05-21

**Keywords:** Knee osteoarthritis, Metformin, Randomized controlled trial

## Abstract

**Background:**

Osteoarthritis (OA) is the most common joint disease, and is most frequently seen in the knees. However, there is no effective therapy to relieve the progression of knee OA. Metformin is a safe, well-tolerated oral medication that is extensively used as first-line therapy for type 2 diabetes. Previous observational studies and basic researches suggested that metformin may have protective effects on knee OA, which needs to be verified by clinical trials. This study, therefore, aims to examine the effects of metformin versus placebo on knee cartilage volume loss and knee symptoms in overweight knee OA patients by a randomized controlled trial over 24 months.

**Methods:**

This protocol describes a multicenter, randomized, double-blind, and placebo-controlled clinical trial aiming to recruit 262 overweight knee OA patients. Participants will be randomly allocated to the two arms of the study, receiving metformin hydrochloride sustained-release tablets or identical inert placebo for 24 months (start from 0.5 g/day for the first 2 weeks, and increase to 1 g/day for the second 2 weeks, and further increase to 2 g/day for the remaining period if tolerated). Primary outcomes will be changes in tibiofemoral cartilage volume and Western Ontario and McMaster Universities Osteoarthritis Index (WOMAC) score over 24 months. Secondary outcomes will be changes in visual analogue scale (VAS) knee pain, tibiofemoral cartilage defects, effusion-synovitis volume, and tibiofemoral bone marrow lesions maximum size over 24 months. The primary analyses will be intention-to-treat analyses of primary and secondary outcomes. Per-protocol analyses will be performed as the secondary analyses.

**Discussion:**

If metformin is proved to slow knee cartilage volume loss and to relieve knee symptoms among overweight knee OA patients, it will have the potential to become a disease modifying drug for knee OA. Metformin is a convenient intervention with low cost, and its potential effects on slowing down the structural progression and relieving the symptoms of knee OA would effectively reduce the disease burden worldwide.

**Trial registration:**

ClinicalTrials. gov NCT05034029. Registered on 30 Sept 2021.

## Background

Osteoarthritis (OA) is one of the most common joint diseases worldwide, and knee is the most commonly affected joint [1]. It leads to joint pain and physical disability, decreases mobility and quality of life, and is the major cause of the increasing demand for joint replacement [2–4]. Currently, more than 300 million people suffering from OA worldwide [5]. In the population over 50 years of age, the prevalence of OA is up to 10-20% [6]. OA has a huge economic burden, and its social cost could account for 0.25-0.5% of a country’s gross domestic product (GDP) [7]. Moreover, due to the increased proportion of the elderly and obese people in the population, the incidence of OA is expected to increase further [3]. However, there has been no disease-modifying OA drug approved by the regulatory bodies at present [2]. Thus, there is an urgent need to find drugs that can effectively modify the progression of OA.

Metformin is a safe, well-tolerated oral medication that is widely used as the first-line therapy for type 2 diabetes [8]. In recent years, metformin has attracted extensive attention for its potentially multiple effects such as weight reduction, anti-inflammatory, anti-oxidant, and anti-aging [9–12]. Given the biological effects of metformin and the important roles of overweight, inflammation, oxidative stress, and aging playing in knee OA, metformin might be a potential disease modifying agent for knee OA, especially for those with the obese phenotype [13].

Indeed, accumulating evidences suggest that metformin may have OA protective effects. A study reported that metformin administered intragastrically in destabilization of the medial meniscus (DMM) mouse model of knee OA could maintain the balance of chondrocyte synthesis and catabolism, delay cartilage aging and the progression of knee OA by regulating the AMP-activated protein kinase (AMPK) /mammalian target of rapamycin (mTOR) signaling pathway [14]. Similar to this study, another study demonstrated that intraarticular injections of metformin in DMM-induced OA mice mitigated cartilage degradation by activating AMPK/the specifically silent information regulator 1 (SIRT1)-mediated autophagy [15]. Besides, the cartilage protective effect of metformin was also confirmed in both collagenase-induced and papain-induced OA mouse models [16, 17]. Three other in vivo studies demonstrated that metformin also had an analgesic effect along with the joint structure-protective effects. One study showed that both intragastric and intraarticular administration of metformin attenuated articular cartilage degradation and modulated pain-related behavior in DMM-induced OA mouse model [18]. In a monosodium-iodoacetate-induced OA rat model, oral administration of metformin reduced the OA-related pain as well as bone and cartilage damage of the joint [19]. Another animal study reported that oral metformin could inhibit articular cartilage degeneration, synovial hyperplasia, osteophyte formation, and OA-related pain in DMM-induced OA mouse model by activating the AMPK signaling pathway, and the protective effects of metformin on knee OA were also confirmed in non-human primates [20]. The beneficial effect of metformin on OA was also implied by epidemiological studies. A retrospective study reported that OA patients with type 2 diabetes receiving a combination of metformin and cyclooxygenase-2 (COX-2) inhibitors had a lower rate of joint replacement than those receiving COX-2 inhibitors alone [21]. Another prospective cohort study reported metformin usage was associated with a lower rate of medial cartilage volume loss and a trend of reduced risk of total knee replacement in individuals with knee OA and obesity [22].

Thus, experimental and epidemiological evidence suggested that metformin could be repurposed for the management of knee OA. However, there is no clinical trial with high-level evidence supporting this idea. Therefore, we purpose to conduct a randomized, double-blind, and placebo-controlled trial to examine the structure-modifying and symptom-relieving effects of metformin on knee OA.

The objective of this study is to compare, in a randomized, double-blind, and placebo-controlled trial over 24 months, the effect of metformin versus placebo on knee structural changes and knee symptoms in 262 overweight knee OA patients. The primary hypotheses of this trial are that metformin will reduce the loss of tibiofemoral cartilage volume and Western Ontario and McMaster Universities Osteoarthritis Index (WOMAC) score over 24 months compared with placebo in overweight knee OA patients. The secondary hypotheses are that metformin will reduce the visual analogue scale (VAS) knee pain, tibiofemoral cartilage defects, effusion-synovitis volume, and tibiofemoral bone marrow lesions maximum size over 24 months compared with placebo in overweight knee OA patients. If metformin is proved effective, it will offer a novel approach for knee OA treatment.

## Methods/design

### Study design

This study is designed as a multicenter, randomized, double-blind, placebo-controlled trial over 24 months. Two hundred and sixty-two symptomatic knee OA patients with overweight will be recruited and randomly allocated to either the treatment or placebo control group. The recruitment strategy will include collaborations with specialist rheumatologists, orthopedic surgeons, rehabilitation physicians, and general practitioners, as well as advertising through posters and social media. The primary site of this trial is Guangzhou First People’s Hospital with ethics approval being received from the Ethics Committee of Guangzhou First People’s Hospital (reference number: K-2021-001-02). The sub-sites initially include: Sun Yat-sen Memorial Hospital of the Sun Yat-sen University, Zhujiang Hospital of Southern Medical University, Foshan First People’s Hospital, Liwan Central Hospital of Guangzhou, the Third People’s Hospital of Shenzhen and the Second Affiliated Hospital of Nanchang University. Ethics approval will be received from each of the institutions before the recruitment. Competitive enrollment will be adopted among study sites. Informed written consent will be obtained from all participants. Reporting of the trial will be guided by the Consolidated Standards of Reporting Trials (CONSORT) Statement [23]. The study design of this trial is depicted by Fig. 1.

**Fig. 1 Fig1:**
[figure not shown]
Flowchart of the trial. ^#^MRI, questionnaires, and body composition will be acquired. ^☩^262 participants will be enrolled and equally allocated to the two groups (131 per group) in this trial; however, the number of participants actually enrolled may vary slightly. ^*^The follow-up will be carried out at 3, 6, 12, and 24 months, with questionnaires and body composition being acquired at 3, 6, 12, and 24 months, hematological measurements being acquired at 6, 12, and 24 months, and MRI being acquired at 24 months

### Inclusion criteria

Meet the American College of Rheumatology (ACR) criteria for symptomatic knee OA [24], assessed by a rheumatologist;Age 50 to 75 years;Body mass index (BMI) ≥ 24 kg/m^2^;Knee pain ≥20 on a 100 mm VAS;Being able to listen, speak, read and understand Chinese, capable of understanding the study requirements and willing to cooperate with the study instructions, and able to provide written informed consent.

### Exclusion criteria

Severe radiographic knee OA as grade 3 joint space narrowing according to the Osteoarthritis Research Society International (OARSI) atlas [25];Severe knee pain as knee pain ≥80 on a 100 mm VAS;Planned knee or hip surgery (including arthroscopy, joint replacement, and joint open operation) within 2 years;Severe knee trauma history (including arthroscopy, severe injury of knee ligament or meniscus);Contraindication to magnetic resonance imaging (MRI) scanning (e.g., implanted pacemaker, artificial metal valve or cornea, aneurysm clipping surgery, arterial dissection, metal foreign bodies in the eyeball, claustrophobia);Other forms of inflammatory arthritis (e.g., rheumatoid arthritis, psoriatic arthritis);Active malignant cancer or other life-threatening diseases;Type 1 or type 2 diabetes mellitus;Clinical manifestation of liver dysfunction or elevated alanine aminotransferase/aspartate aminotransferase levels exceeding 2 times the upper limit of normal values;Estimated glomerular filtration rate of less than 60 ml/min/1.73 m^2^;Hypoxic state (e.g., chronic heart insufficiency, acute myocardial infarction, heart failure, chronic obstructive pulmonary disease, cor pulmonale, peripheral vascular disease);Alcoholism;Pregnancy or lactation;Allergic to metformin hydrochloride;Conditions affecting the absorption of oral drugs (e.g., postgastrectomy and malabsorption syndrome);Use of metformin in recent 30 days or plan to use metformin in the next 2 years;Use of investigational drug in recent 30 days.

Note: when both knees of the participants meet the eligibility criteria, the knee with more severe VAS pain will be selected as the study knee.

### Randomization and blinding

To control for variation in study sites, the randomization will be stratified by the study sites. Participants in each site will be randomly assigned to the intervention arm or placebo arm in a ratio of 1:1 based on computer generated random numbers using block randomization (with a block size of 6). Participants, investigators, outcome assessors, as well as statisticians will be blinded to the group allocation in this trial. Allocation concealment will be ensured by keeping the allocation data confidential and using the visual- and taste-masked inert placebo. Emergency unblinding will be permissible when a serious adverse event happens. Participants who are unblinded will be withdrawn from the trial.

### Intervention

Participants in the intervention arm and control arm will take metformin hydrochloride sustained-release tablet (ingredients: microcrystalline cellulose, hydroxypropyl methylcellulose, magnesium stearate, and metformin hydrochloride; Jiangsu Deyuan Pharmaceutical Co., Ltd.) and the identical inert placebo (ingredients: microcrystalline cellulose, hydroxypropyl methylcellulose, magnesium stearate, and lactose; Jiangsu Deyuan Pharmaceutical Co., Ltd.), respectively. The drug and placebo will be administered orally in escalating doses to reduce side-effects and maintain masking: 0.5 g/day for the first 2 weeks, 1 g/day for the next 2 weeks, and then 2 g/day for the remaining period if tolerated. If the subject cannot tolerate the maximum dose (2 g/day), she/he can take their maximum tolerable dose. In case of adverse reaction or deteriorated hepatic and renal function, the researchers can determine whether the subject needs to reduce or stop the drug based on their discretion.

### Quality assurance

Ahead of the recruitment, all research staff will be provided with a standard protocol, a manual of operating procedures (MOP), and a case report form, and will be trained to competently administer all items including questionnaires/surveys, imaging examinations, blood taking, etc. During the study, the project manager will visit each site to monitor trial procedures to ensure the trial is conducted in accordance with the protocol and MOP.

### Outcome measures

Primary outcomes will be changes in tibiofemoral cartilage volume and WOMAC score over 24 months. Secondary outcomes will be changes in VAS knee pain, tibiofemoral cartilage defects, effusion-synovitis volume, and tibiofemoral bone marrow lesions maximum size over 24 months.

#### Assessment of knee structures

Knee structural changes will be assessed using MRI at baseline and 24-month follow-up (Table 1). MRI sequences sensitive for cartilage [e.g., 3D dual-echo in steady state (DESS) or 3D Water Selected fluid (WATSf) sequences] will be used to assess tibiofemoral cartilage volume. MRI sequences sensitive for detailed anatomy [e.g., 2D intermediate-weighted fat suppression or 2D proton density-weighted fat suppression sequences] will be used to assess tibiofemoral cartilage defects, effusion-synovitis volume, and tibiofemoral bone marrow lesions maximum size. All these knee structures will be assessed on the sagittal images. Besides, coronal sequences sensitive for detailed anatomy will be also acquired to assist sagittal images positioning. Details of MRI sequences and parameters will be determined according to the magnetic resonance (MR) scanner available at each site. Before the enrollment, the specific MRI sequences and parameters will be tested in corresponding MR scanners to ensure the MR image meets the study requirement.

**Table 1 Tab1:** Schedule of data collection

	Screening	months				
		0	3	6	12	24
**Primary outcomes**						
Tibiofemoral cartilage volume		✔				✔
WOMAC		✔	✔	✔	✔	✔
**Secondary outcomes**						
Knee pain VAS	✔	✔	✔	✔	✔	✔
Tibiofemoral cartilage defect		✔				✔
Effusion-synovitis volume		✔				✔
Tibiofemoral bone marrow lesion maximum size		✔				✔
**Other measurements**						
Clinical evaluation and history inquiry	✔					
Joint space narrowing	✔					
Hepatic and renal function	✔			✔	✔	✔
Height	✔					
Weight	✔	✔	✔	✔	✔	✔
Hoffa-synovitis		✔				✔
AQoL-4D		✔	✔	✔	✔	✔
PHQ-9		✔	✔	✔	✔	✔
Body composition		✔	✔	✔	✔	✔
Serum cytokines	✔					✔
Foot pain VAS		✔	✔	✔	✔	✔
Low back pain VAS		✔	✔	✔	✔	✔
Concomitant medication		✔	✔	✔	✔	✔
Pill counts		✔	✔	✔	✔	✔
Adverse events		✔	✔	✔	✔	✔

*WOMAC* Western Ontario and McMaster Universities Osteoarthritis Index, *VAS* visual analogue scale, *AQoL-4D* four-dimensional Assessment of Quality of Life, *PHQ-9* nine-items Patient Health Questionnaire

Cartilage volume will be semi-automatically calculated based on a standardized view of 3D cartilage geometry by OsiriX software (University of Geneva, Geneva, Switzerland). The 3D cartilage geometry is composed from the 2D cartilage shapes, which are generated by drawing contours around the cartilage boundaries on section-by-section MR images [22]. Tibiofemoral cartilage volume will be calculated as the sum of both the tibial and femoral compartments.

Cartilage defects will be graded using a modified Outerbridge classification as follows: grade 0, normal cartilage; grade 1, normal contour but focal blistering and intra-cartilaginous hyperintensity; grade 2, irregularities on the surface with loss of thickness of less than 50%; grade 3, deep ulceration with loss of thickness of more than 50% but no exposure of subchondral bone; grade 4, full-thickness chondral wear with exposure of subchondral bone [26]. Cartilage defects will be assessed at the medial tibial, medial femoral, lateral tibial, and lateral femoral compartments, and tibiofemoral cartilage defects will be obtained by summing the scores of the four compartments.

Effusion-synovitis volume will be measured at suprapatellar pouch, central portion, posterior femoral recess, and subpopliteal recess according to the anatomy of the knee joint synovial cavity. Effusion synovitis will be isolated by selecting a region of interest with an intra-articular fluid-equivalent signal on the section-by-section 2D MR images [26]. The volume of effusion-synovitis will be generated using OsiriX software. Total effusion-synovitis volume of the knee will be obtained by summing the volume of possible effusion synovitis in the four synovial cavities.

Bone marrow lesions is defined as discrete areas of increased signal in the subchondral bone. Bone marrow lesions maximum size will be assessed at the medial tibial, medial femoral, lateral tibial, and lateral femoral compartments. Slice with the greatest area of bone marrow lesions in a specific compartment will be chosen to assess bone marrow lesions maximum size of the corresponding compartment. Bone marrow lesions on adjacent slices will be measured and compared to locate the slice with the maximum lesion size [27]. Tibiofemoral bone marrow lesions maximum size will be calculated by summing the maximum lesions size of the four compartments.

#### Assessment of knee symptoms

Knee symptoms will be assessed by WOMAC score and VAS knee pain at baseline and 3-month, 6-month, 12-month, and 24-month follow-up (Table 1).

The WOMAC system in a 100-mm visual analog format will be used to quantify the degree of knee pain (5 questions), joint stiffness (2 questions), and physical dysfunction (17 questions) during the last 7 days [26]. The WOMAC score will be calculated by summing the score of each question (1 point for every 1 mm), and a higher score of WOMAC represents a more severe OA symptom. The WOMAC score will be considered invalid and treated as missing data if more than 5 of the questions are not answered. In case no more than 5 items are missed, the remaining items will be averaged and then multiplied by 24 to create the WOMAC score.

The 100 mm VAS will be used to assess the knee pain during the last 7 days, and a higher VAS indicates a more severe knee pain.

#### Other measurements

Several other measurements will be performed as follows (Table 1).

Clinical evaluation and history inquiry: clinical evaluation and history inquiry will be conducted for the participant screening.

Joint space narrowing: joint space narrowing will be assessed by a standing anteroposterior semiflexed radiograph of the study knee. X-rays will be scored for joint space narrowing on a four points scale (0-3) using the OARSI atlas [25].

Height: Height will be measured to the nearest 0.1 cm (with shoes removed) using stadiometers.

Weight and body composition: weight and body composition (e.g., fat mass, skeletal muscle mass, and visceral fat mass) will be assessed using bioelectrical impedance analyses.

Hoffa-synovitis: Hoffa-synovitis is defined as discrete areas of increased signal within the infrapatellar fat pad on fat-suppressed water sensitive MRI sequences and will be assessed on the sagittal intermediate-weighted/proton density-weighted sequences according to the following grades: grade 0, none; grade 1, less than 10% of the region; grade 2, 10-20% of the region; and grade 3, more than 20% of the region [28].

Quality of life: The four-dimensional Assessment of Quality of Life (AQoL-4D) questionnaire will be used to assess the quality of life during the last 7 days. AQoL-4D comprises four dimensions of independent living, social relationships, psychological well-being, and physical senses, and each dimension has three items with four levels of severity. The total sum scores range from 0 to 36, and a higher score of AQoL-4D represents a lower quality of life [26].

Depressive symptoms: The nine-items Patient Health Questionnaire (PHQ-9) will be used to assess depressive symptoms during the last 2 weeks. All nine items of the PHQ-9 have four response categories scored from 0 to 3. The total sum scores range from 0 to 27, and a higher score indicates more severe depressive symptoms [26].

Foot pain: The 100 mm VAS will be used to assess the foot pain during the last 7 days, and a higher VAS indicates a more severe foot pain.

Low back pain: The 100 mm VAS will be used to assess the low back pain during the last 7 days, and a higher VAS indicates a more severe low back pain.

Hematological measurements: Fasting morning blood samples will be collected at the screening and 6, 12, 24-month follow-up. Serum levels of alanine aminotransferase and aspartate aminotransferase and estimated glomerular filtration rate will be tested at the above time points to reflect the hepatic and renal function. Besides, at the screening and 24-month follow-up, blood lipid profile and C-reactive protein will be tested and serum will be isolated and stored at − 80 °C for further measurement of inflammatory cytokines (e.g., tumor necrosis factor**-**α, interleukin-1, interleukin-6) and adipokines (e.g., leptin, resistin, visfatin).

Concomitant medication: Concomitant medication usage will be not restricted in this study, but will be documented at the baseline and each follow-up.

Pill counts: The pill counts will be recorded to infer the medication compliance of the participants.

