### Statistical analysis plan

Baseline characteristics will be reported per group using descriptive statistics (means, proportions, and medians as appropriate) without statistical tests.

The primary analyses will be intention-to-treat analyses of primary and secondary outcomes. Per-protocol analyses will be performed as the secondary analyses, and participants with an average daily dose of 0.5-2 g of the investigational drug will be included in the per-protocol analyses. Missing data caused by loss to follow-up and nonresponses will be addressed by multiple imputations with chained equations. Imputations will be performed separately for each treatment group and each outcome using baseline variables of age, sex, BMI, and study site and non-missing values of the outcomes at baseline and each follow-up with the assumption of data missing at random. The treatment effect will be analyzed using linear mixed effect models. In the models, baseline covariates (age, sex, BMI, baseline value of the corresponding outcome), treatment, month, and the interactions of covariates and treatment with month will be entered as fixed effects. The correlation within the study sites and the repeated measures will be addressed using trial site and participant identification as random intercepts. Month will be treated as random slope to allow different treatment effects among knee OA patients over time. Changes in outcome measures within each group and difference of the changes between groups from baseline to follow-up will be calculated using linear combinations of the estimated coefficients.

Pre-specified stratified analyses will be performed to explore whether BMI could affect the treatment effect of metformin on knee OA. This will be conducted by introducing a 3-way interaction between treatment, month, and BMI in the linear mixed-effects models.

Because of the potential for type I error due to multiple comparisons, the findings for the analyses of the secondary outcomes and the stratified analyses will be interpreted as exploratory. A 2-sided *P* value of 0.05 or less will be considered as statistically significant.

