### Withdrawal

If participants withdraw from the study before the end of the trial, the reason and date will be recorded. Participants who withdraw from the trial after 6 months of follow-up will be asked to have the final assessments at the 24-month follow-up. Outcomes assessed before the withdraw and at the 24-month follow-up will be used for the statistical analyses.

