### Data integrity and management

All data obtained will be kept strictly confidential and will be stored electronically on a database with secured and restricted access (Research Electronic Data Capture, REDCap). After each follow-up, the obtained data will be timely inputted into the electronic database. The entered data will be routinely checked to correct the potential mistaken input. The obtained MR images will be stored electronically and transferred to the sponsor (Guangzhou First People’s Hospital) in time. At the completion of the follow-up, the MR images will be uniformly assessed and the acquired data will be inputted into the electronic database at the primary site. Then, all the data will be checked and locked. After that, a two-step unblinding method will be applied. The first step of the unblinding will classify the participants to group A and group B for efficacy endpoints and safety analyses. When the analyses are completed, the second step of the unblinding will be conducted to assign group A and group B.

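### Metformin is not excepted from the unrestricted-medication rule, so it may be added to blinded study drug, and a placebo participant who adds it can stay a per-protocol control (minor; mainly a safety safeguard)

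*Protocol article*

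**What the plan says.** All references are to the protocol article.

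- **At entry.** Exclusion criteria removes people with "Use of metformin in recent 30 days or plan to use metformin in the next 2 years", and also people with type 1 or type 2 diabetes.
- **On study.** Other measurements, under concomitant medication: "Concomitant medication usage will be not restricted in this study, but will be documented at the baseline and each follow-up". No drug is excepted.
- **Dose.** Intervention titrates to 2 g/day and treats that as the ceiling: "If the subject cannot tolerate the maximum dose (2 g/day), she/he can take their maximum tolerable dose".
- **Reducing or stopping.** The same section: "In case of adverse reaction or deteriorated hepatic and renal function, the researchers can determine whether the subject needs to reduce or stop" the drug, at the researchers' discretion.
- **Unblinding.** Randomization and blinding: "Emergency unblinding will be permissible when a serious adverse event happens. Participants who are unblinded will be withdrawn from the trial".
- **Per-protocol set.** Statistical analysis plan: "participants with an average daily dose of 0.5-2 g of the investigational drug will be included in the per-protocol analyses". No other criterion is stated.
- **Follow-up after withdrawal.** Withdrawal: "Participants who withdraw from the trial after 6 months of follow-up will be asked to have the final assessments at the 24-month follow-up".

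**The concern.** The entry criterion covers the full two years of treatment, so the sponsor evidently wanted outside metformin kept out of the trial. But it screens only a plan held at entry. A prescription written later, for instance after newly diagnosed diabetes, falls under the on-study rule, and that rule allows it.

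Two things follow. The first concerns safety: someone on blinded metformin at full dose may take more on top, and nothing stated requires the study tablets to be stopped first. The second concerns the per-protocol analysis: its one stated criterion looks at the amount of study drug taken and not at outside metformin, so a control who is taking the test drug can stay in the comparison. Such controls pull that contrast toward zero.

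**Working it through.** **Inputs from the document.** WOMAC difference 159.92, SD 413.74, 105 per group before dropout, 20% dropout (Sample size); dose steps 0.5, 1 and 2 g/day, the first two lasting 14 days each (Intervention).

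**Assumptions.** The share p of placebo participants who add metformin is not given; 1%, 2% and 5% are used. The fraction f of the full effect they obtain is set at 0.5 (a mid-trial start) or 1. Study-drug dose is taken to count assigned tablets, placebo included, averaged over 730 days.

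**1. The plan's own figure.** 2 × [(1.96 + 0.842) × 413.74 / 159.92]² = 105.1, against the stated 105; 105 / 0.8 = 131.25, against the stated 131. The inputs reproduce. SE of the contrast with 105 per arm: 413.74 × √(2/105) = 57.1.

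**2. Combined dose in the active arm.** Adding the protocol's own dose steps, as illustrations, to 2 g/day: 2 + 0.5 = 2.5, 2 + 1 = 3, 2 + 2 = 4 g/day. Each exceeds 2 g/day.

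**3. Does a placebo participant who adds metformin meet the per-protocol criterion?** Full adherence gives 14 × 0.5 + 14 × 1 + 702 × 2 = 1425 g, and 1425 / 730 = 1.95 g/day, inside 0.5–2. Someone who stops study tablets part-way can also stay inside. The lower limit needs 0.5 × 730 = 365 g; 21 g is taken by day 28, and (365 − 21) / 2 = 172 more days, so the limit is reached on day 200. Stopping tablets after that does not by itself remove the person from the set.

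**4. Effect of keeping such controls.** Shrinkage = 159.92 × p × f.

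| p | f = 0.5 | f = 1 |
|---|---|---|
| 1% | 0.8 | 1.6 |
| 2% | 1.6 | 3.2 |
| 5% | 4.0 | 8.0 |

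The largest is 8.0 / 57.1 = 0.14 SE.

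**5. Effect of excluding them.** Let D be the users' minus the non-users' WOMAC change had neither taken metformin (positive = worse). With exclusions in the placebo arm only, the contrast becomes 159.92 − p × D. At p = 5%, D = +80 gives 155.9 and D = −80 gives 163.9; keeping them at f = 0.5 gives 159.92 − 4.0 = 155.9. Exclusion is less biased than keeping while |D| < f × 159.92, that is 80 points (80 / 413.74 = 0.19 SD) at f = 0.5 or 160 points (0.39 SD) at f = 1. The SE, 413.74 × √(1/105 + 1/[105(1 − p)]), rises from 57.1 to 57.2, 57.4 or 57.8 for p = 1%, 2% or 5%.

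**The case against.** The strongest reply has four parts.

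*The sentence is a data-collection line.* It sits among recorded measurements and was probably written with analgesics and background drugs in mind. That may well be the intent, but the wording is general and is the only on-study medication rule given. It is a stated rule, so this is not a detail that the article has left to another document.

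*The provisions on unblinding and stopping do not forbid sensible action.* A reader might infer that unblinding is possible only after a serious adverse event, that tablets may be stopped only after an adverse reaction or worse hepatic or renal function, and so that an investigator is trapped. The document does not support this. Both sentences are permissive, neither says that it is exhaustive, and an investigator could stop tablets when metformin is needed. Nor does avoiding duplicate dosing require knowledge of the allocation. What stands is narrower: no stated rule requires the tablets to be stopped.

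*No harm is shown.* A reader might take 2.5 to 4 g/day as toxic. The document gives no toxicity threshold; 2 g/day is the top of the study titration. Adverse events and concomitant medication are recorded at each visit, and hepatic and renal function is tested at 6, 12 and 24 months. This part stands: the arithmetic shows a dose above the protocol's own ceiling and does not measure risk.

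*The per-protocol half is weak.* The criterion is not said to be the sole one, the control-arm reading is an assumption, the analysis is secondary, and exclusion can bias as much as keeping (step 5). All of this stands as a limit on size. Still, nothing stated removes a control for taking the test drug.

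**Conclusion.** The point holds, as a minor one. The on-study medication rule permits the test drug to be added to blinded treatment, against the evident purpose of the entry criterion, and nothing stated requires study tablets to stop when that happens. The main reason to act is participant safety.

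The number affected is unknown and probably small: diabetes and planned metformin use are excluded at entry, and the follow-up schedule lists no glucose or HbA1c test that would bring new diabetes to light. The statistical effect is small even under generous assumptions, at most about 0.14 SE of the per-protocol WOMAC contrast at 5% with full effect. This rests on the assumed shares and on counting placebo tablets toward the dose criterion.

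A reader might infer that the primary result or the sample size is undermined by the per-protocol rule. It is not: the intention-to-treat analysis keeps these participants whatever that rule says. Nor should the remedy be read as restoring the full per-protocol contrast; that would need the exclusions to be unrelated to outcome.

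**What to change.** **Other measurements (concomitant medication).** Except non-study metformin, alone or in a combination product, from the unrestricted rule. If it becomes clinically necessary, stop study tablets without routine unblinding (unblinded participants are withdrawn) and continue follow-up to 24 months. Say that this is stopping tablets and not withdrawal, because the Withdrawal section asks for the final assessment only from those who leave after 6 months.

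**Statistical analysis plan.** Exclude from the per-protocol set participants in either arm with recorded non-study metformin use. Fix the list before the step at which "The first step of the unblinding will classify the participants to group A and group B", report the frequency by arm, and keep these participants in the intention-to-treat analysis. This clause is needed as well as the first, since stopping tablets after about day 200 leaves the dose criterion satisfied.

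**Cost.** A few sentences and no new data, because concomitant medication is already recorded at baseline and every follow-up. If made after approval, it is an amendment for the ethics committees of the primary site and up to six sub-sites. The per-protocol set becomes slightly smaller, and the exclusion is made after randomisation, may be uneven between arms and may be related to outcome, so the per-protocol result should stay secondary.
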